##### Technical Details of the App.

The mobile app will be initially developed for the Android platform. Future iterations will include an iOS platform. Focusing on one operating system will allow us to develop a self-management mobile app using the highest-quality control standards. We have selected Android because it is the world’s most popular platform [38]. Mobile phones will be provided to any participant who does not have a phone or one compatible with the app. The app will feature separate and secure log-in mechanisms for the adolescent user and parent user. All data will be stored on a remote encrypted server rather than the phone itself. If the phone is lost or stolen, we will have the ability to remotely erase the phone’s contents and turn off the data plan associated with it. Technical specifications and functions of the app have been presented in Textboxes 2 and 3.

### Phase 2: Intervention Study Methods

This portion of the intervention involves having the adolescents and their parents use the app over the course of 3 months.

#### Study Setting

Recruitment will take place in the Sparrow Hospital’s Pediatric Subspecialty Clinic in Lansing, Michigan, United States. The Sparrow Endocrinology Clinic team consists of 1 registered pediatric dietitian, 1 full-time nurse practitioner, 2 certified diabetes educators, and 2 endocrinologists, all of whom provide diabetes care 4 days per week within the larger subspecialty clinic. All patients are scheduled to come to the clinic every 3 months for care.

#### Sample and Recruitment of Participants.

The clinic nurse diabetes educator will act as the site coordinator. Participants for the pilot testing will be recruited from the hospital’s Pediatric Endocrinology Clinic. Invitations will be mailed three times over 2 months to all of the potential participant dyads, as identified by hospital providers. Additionally, the health care providers in the clinics will be given a presentation on the study by the researchers so they can offer it to the families who meet the inclusion criteria during any typical interactions they have with the adolescent and parent.

Technical specifications.Operating system: AndroidData storage: Remote encrypted serverLog-in mechanisms: Separate and secure log-in mechanisms for the adolescent user and parent user

App functions. BG: blood glucose.
**Child functions:**
Incentivized through the use of points accumulated based on usageSend messages via the app to their parentCustomizable test reminders and BG rangesAn educational componentA moderated forum for the adolescents and the parents (separate forums) to post and discuss questions and comments to peers
**Parent functions:**
Review their child’s history of BG values, carbohydrate intake, and physical activity from their own phoneSend messages via the app to their childCustomizable test reminders and BG rangesAn educational componentA moderated forum for the adolescents and the parents (separate forums) to post and discuss questions and comments to peers

Inclusion criteria.
**Adolescents must:**
Have a type 1 diabetes mellitus (T1DM) diagnosis according to the American Diabetes Association practice guidelines [34]Be 10-15 years oldHave had a diagnosis of T1DM for at least 6 months; have glycated hemoglobin>7 [35]Have had at least two outpatient visits in the past 2 yearsBe treated at the local clinic for diabetesBe fluent in EnglishHave a parent or guardian willing to participateBe allowed to use a mobile phone for the studyHave permission from their care team
**Parents must:**
Have an adolescent with T1DM who is 10-15 years oldBe fluent in EnglishAnd have daily access to email and the internet (for appointment reminders and technical support)

Exclusion criteria.
**Adolescents:**
With a diagnosis of a major psychiatric or neurocognitive disorder (eg, traumatic brain injury, dementia, schizophrenia, bipolar disorder, borderline personality disorder, and intellectual disability)With significant medical conditions other than type 1 diabetesBeing treated for thyroid disorders, celiac disease, or eating disordersIn foster care
**Parents:**

With a diagnosis of a major psychiatric or neurocognitive disorder (eg, traumatic brain injury, dementia, schizophrenia, bipolar disorder, borderline personality disorder, and intellectual disability)

If interested, the parent will contact the researchers to learn more about the study. A researcher will be in the waiting room of the pediatric endocrinologists, providing study information to possible participants. The researcher will explain the study and determine if the adolescent and parent are eligible through a brief screening questionnaire. We will recruit a total of 70 adolescent and parent dyads, which would correspond to similar past research studying T1DM and mobile phone interventions [12]. Inclusion and exclusion criteria have been presented in Textboxes 4 and 5, respectively.

#### Study Procedures.

During the study, there will be 4 contact points with the participants: the enrollment or baseline data collection visit (Visit 1), a midpoint review (Visit 2, 3 months after Visit 1), an end-of-study visit (Visit 3, 6 months after Visit 1), and a follow-up visit 3 months after app usage has stopped (Visit 4). Visit 1 (month 0) will be scheduled during the screening process. At Visit 1, a member of the research team will review and obtain informed consent (parent) and assent (adolescent) from the participants. The participants will then complete the baseline surveys to measure self-efficacy, quality of life, and social support and conflict; the laboratory will test the teens’ HbA_1c_, and we will download data from their glucometer or pump. If a participant does not have a mobile device that can download and operate the app, the research team will provide the participant with a device and data plan for the duration of the study. The researcher will demonstrate how to use the technology and have the participants use each of the functions. At Visit 2 (month 3), a research team member will test the adolescents’ HbA_1c_ and download data from their glucometer or pump. The participants will also complete the survey at the midpoint. The midpoint data will be used to demonstrate whether any change at 6 months is part of an increasing trend, a plateau, or a waning trend. At Visit 3 (month 6), the participants will complete the survey and participate in interviews. Additionally, the adolescents’ HbA_1c_ will be tested, and the meter or pump readings will be collected. Finally, any participant that has borrowed any equipment will need to return it at this time. Qualitative methods will also be used to better examine perceptions and intentions, whether participants were light users, or why participants dropped out of the study [39]. After Visit 3, the participants will not use the app for 3 months. At Visit 4 (month 9), all the participants will complete the survey. The researchers will test the adolescents’ HbA_1c_ and download data from their glucometer or pump.

#### Outcome Measures

Specifically, the aim 2 seeks to determine the feasibility and impact on diabetes of the self-management mobile app among the adolescents and their parents. Demographic information will also be collected including current age, age at diagnosis, race, gender, parental status (ie, mom, dad, stepdad, etc), and method of diabetes treatment (eg, pump).

Hypothesis 1 seeks to demonstrate that adherence to self-management correlates with mobile app usage and a decrease in HbA_1c_. HbA_1c_ data will be collected through the hospital laboratory system. The patient will be provided with a laboratory slip to obtain the baseline HbA_1c_ value. The patient will be instructed to obtain the lab results within 1 week. Once the results are obtained, they will be faxed to the principal investigator via a secure fax line. Adherence will be measured in two ways. First, the participants will complete the Diabetes Behavior Rating Scale [40]. Second, we will use data from the server to determine if they are monitoring blood sugar on schedule and what mechanisms of the app helped the adolescents follow the medical recommendations. For example, we will use time-stamped log-ins, number of sections the user visited, number of individual logs, communication through the app, educational information accessed, and duration of use per log-on.

Hypothesis 2 states that through use of the app, the participants’ self-efficacy [29,41,42], quality of life [43-45], and perceptions of social support [46-48] will improve, and conflict [49] between the child and parent will be reduced from baseline to 3 months. These secondary outcomes are key in helping the adolescents maintain adherence and a normal HbA_1c_ [50-52] and will be measured through surveys. The survey instruments, the participants who will complete them, and reliability for each measure can be found in Table 2.

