**Phase 2**

*Specific Aim 2: Conduct pilot testing of the self-management mobile app to determine its feasibility and impact on diabetes self-management*
H1 (primary outcomes): Measures of app usage will be associated with increased adherence to self-management and lower glycosylated hemoglobin.H2 (secondary outcomes): Measures of app usage will be associated with increased quality of life, self-efficacy, and social support and decreased conflict between the adolescents and their parents.

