#### The Mobile App

##### App Functionalities

The self-management mobile app will be an intervention mechanism to encourage adolescents aged 10 to 15 years to self-manage their diabetes by recording their values while allowing their parents seamless and unobtrusive access to the same blood glucose (BG) values, carbohydrate intake, and physical activity data, which will be time-stamped, encrypted, and sent to a remote server for storage.

**Table 1 table1:** App development benchmarks.

Step	Time (in days)
Server management	13
User management	13
Server side logic	12
Data integration	13
Push logic	6
Versioning	12
Cache logic	6
Synchronization	8
Wireframe development	8
User interface design & development	33

The parent users will have a separate log-in and will be able to review their child's history of BG values, carbohydrate intake, and physical activity from their own phone to help their child make decisions about managing their diabetes. Parents may also send messages via the app to their child. However, the parent can still communicate outside of the app, and we will ask about this communication in the poststudy interviews.

Along with customizable test reminders and BG ranges, the app will also have an educational component and a moderated forum for the adolescents and the parents (separate forums) to post and discuss questions and comments to peers. The adolescents will be incentivized through the use of points accumulated based on usage. These points can be used by the adolescents to purchase accessories for a superhero avatar. As this is a feasibility study, we will have the adolescents manually input their BG readings into the app. While this may seem cumbersome, most meters and pumps do not have the ability to automatically send data through Bluetooth. Once we can determine the feasibility and other design requirements through this pilot, we will develop the app to be Bluetooth-enabled. The participants and their parents are responsible for notifying their medical providers regarding any issues with their diabetes. Our app will not cause an actual health concern, as it is just a monitoring and communication device.

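### The server-based adherence measure comes from the same app logs as the usage measures, so its correlation with usage is positive largely by construction and it has no baseline

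*Protocol article*

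**What the plan says.** The primary hypothesis (Specific aims, Phase 2) reads: "Measures of app usage will be associated with increased adherence to self-management and lower glycosylated hemoglobin". App usage is the predictor; adherence and HbA1c are the outcomes.

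Under Outcome Measures, "Adherence will be measured in two ways". The first way is a questionnaire: "First, the participants will complete the Diabetes Behavior Rating Scale". For the second, "we will use data from the server to determine if they are monitoring blood sugar on schedule" and to learn which app mechanisms helped. The examples that follow are app activity counts: "we will use time-stamped log-ins, number of sections the user visited, number of individual logs, communication through the app", then educational material opened and time spent per log-on.

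Under App Functionalities, "we will have the adolescents manually input their BG readings into the app"; automatic transfer is left to a later version of the app.

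Under Study Procedures, the app is introduced at Visit 1 ("The researcher will demonstrate how to use the technology and have the participants use each of the functions"), and participants are off the app between Visit 3 (month 6) and Visit 4 (month 9). Meter or pump data are downloaded at all four visits.

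Analysis and Statistical Power correlates the usage measures with all study outcomes at each time point and tests the correlations for significance. It then repeats the analysis on change from baseline, including a regression that adjusts for the baseline value.

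**The concern.** A glucose check that is done but not typed in does not exist on the server. There, monitoring on schedule can only mean logging in the app on schedule. An adolescent who tests faithfully but rarely logs is scored both as non-adherent and as a light user. One who logs everything scores high on both. The two variables rise and fall together whether or not the app changes how often anyone tests.

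The measure also does not fit the planned analyses. They need a value at Visit 1 and, for trends over the four visits, one for the period before Visit 4. The server can supply neither.

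At stake is the interpretation of the only adherence measure in Outcome Measures that is not a questionnaire. The article names an effect size for powering a larger study among its main aims, and a full-scale randomised trial is planned next. A correlation produced by shared logs could be carried into that design as evidence of an effect.

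**Working it through.** **1. Sources side by side.**

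| Item | Source in the article | Before the app (Visit 1) | Months 6-9 (Visit 4) |
|---|---|---|---|
| App usage | Server logs | None | None |
| Adherence, first measure | Rating scale | Survey (see objection) | Survey |
| Adherence, second measure | Server logs | None | None |
| HbA1c | Laboratory | Yes | Yes |
| Meter or pump download | Device; not named under adherence | Yes | Yes |

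Only the second adherence measure shares its source with the predictor, and it is the only outcome in the table without a Visit 1 value.

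**2. Size.** The article gives no figure for this correlation, so I simulated it. All inputs except n = 70 and the two-sided 0.05 level are assumptions, not values from the article.

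- 70 adolescents, 90 days, 4 scheduled checks a day; 2,000 simulated studies; Pearson correlation.
- True tests per day: T ~ Poisson(λ), with λ ~ N(4, 1) across adolescents.
- Probability that a completed test is typed in: π ~ Beta(1.5, 1.5), independent of λ. True testing is thus unrelated to willingness to log.
- Entries per day: G ~ Binomial(T, π).
- Server adherence = mean over days of min(G, 4)/4.
- Meter adherence = mean over days of min(T, 4)/4.
- Log-in days = number of days with G > 0.
- Non-glucose usage ~ Poisson(30π).

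For scale, the smallest significant correlation at n = 70 is t/√(t² + n − 2) = 1.995/√(3.98 + 68) = 0.235.

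| Predictor | Adherence outcome | Mean r | Significant |
|---|---|---|---|
| Log-in days (from glucose entries) | Server | 0.92 | 100% |
| Log-in days (from glucose entries) | Meter | 0.33 | 80% |
| Total glucose entries | Meter | 0.42 | 98% |
| Non-glucose usage | Meter | 0.00 | 4% |

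Separate simulation runs of the same comparisons gave 0.34 in place of 0.33, and about 5% in place of 4%.

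**3. Why the second and third rows are not zero.** Expected entries per day are λπ and expected tests are λ. Someone who tests more has more to type in, so usage that counts glucose entries contains λ even when π is independent of it. Moving the outcome to the meter removes only part of the problem; glucose entries must also leave the predictor.

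**4. Sensitivity.** A second set of assumptions used a true on-schedule share with mean 0.70 and SD 0.15 to 0.25, several logging-propensity distributions, and Spearman correlation.

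- Server adherence against usage that counts glucose logs: about 0.99, significant in 100% of runs.
- Server adherence against non-glucose log-ins only: 0.21 to 0.78, significant in 40% to 100% of runs.
- Meter adherence against usage that counts glucose entries: 0.35, significant in 85% of runs (one setting).
- Meter adherence against non-glucose usage: significant in 4.5% of runs.

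The values move with the assumptions. The association returns to the nominal error rate only when both changes are made.

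**The case against.** The strongest reply is that little rests on this measure. The article calls all analyses exploratory and the study an uncontrolled feasibility study. The rating scale and HbA1c do not depend on the server, and Table 2 lists only the rating scale under adherence. This stands as a limit on the consequence. It does not remove the overlap: Outcome Measures names the server as the second adherence measure, the hypothesis is labelled primary, and the correlations are formally tested.

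A second reply is that the list of server counts may describe how the app helped, not adherence itself, since the sentence before it has both purposes. That is fair for sections visited, education and duration, and the article does not say which counts become the usage predictors. But on-schedule monitoring still has to be read from typed entries, and even usage counted without glucose entries correlates with server adherence (0.21 to 0.78 above).

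Two stronger readings are tempting. A reader might infer that the primary hypothesis as a whole would be confirmed even if the app did nothing. The documents do not support this, because the overlap touches one of two adherence measures and not HbA1c. A reader might also infer that adherence has no baseline at all, because the Visit 1 list ("complete the baseline surveys to measure self-efficacy, quality of life, and social support and conflict") omits it. Table 2 puts the rating scale among the survey instruments, Visits 2 to 4 refer to the survey, and change from baseline is planned. An incomplete list is the likelier explanation.

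Finally, a condensed article may leave the processing of meter data to the full protocol. That is possible, and nothing is lost irrecoverably, but the server is what the article names as the source.

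**Conclusion.** The point holds for the server-based adherence measure. Its correlation with app usage is positive largely by construction, and the planned change-from-baseline analysis cannot be run on it, because server data are absent before the app is introduced and for months 6 to 9. The source overlap and the missing baseline follow from the text alone. The sizes (about 0.92 against server adherence, about 0.33 against meter adherence with glucose-based usage, about 0 with non-glucose usage) rest on assumed testing and logging patterns, with true testing set independent of logging. They show direction and rough scale and do not predict this trial's result. The rating-scale and HbA1c results remain interpretable on this score.

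**What to change.** Before analysis, amend Outcome Measures as follows:

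1. Define objective monitoring adherence from the meter or pump downloads at Visits 1 to 4, for example as the share of scheduled checks done. This gives a baseline and a month 9 value.
2. Use server data only as the usage predictor.
3. For this analysis, define usage from non-glucose activity: sections visited, messages sent, education opened, and log-ins without a glucose entry.
4. Report glucose entries typed into the app as engagement, not as adherence.
5. As a minor wording point, name the Diabetes Behavior Rating Scale in the Visit 1 survey list so that it agrees with Table 2.

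The cost is revised wording and some processing of data already collected; no new visit or measurement is needed. The drawback is that device memory may cover only part of each interval, so the window that each download represents should be stated.

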#### Analysis and Statistical Power

This is a feasibility study, so all analyses will be exploratory, focusing on identifying temporal trends in the self-management mobile app usage and changes in study outcomes and identifying associations between outcomes. Preceding the analyses, we will calculate summary statistics for all measures as well as exploratory plots (histograms and box-plots) for all measures at each time point to identify outliers and potentially spurious values.

Trends over the 4 visits will be examined graphically as a function of time using nonparametrically smoothed plots to help identify when potential effects reach their maximum, plateau, and begin to decrease, which may indicate a time to target for additional interventions. At each time point, we will calculate pairwise correlations between the self-management mobile app usage measures and all study outcomes and examine bivariate scatter-plots with estimated trends for each pair. Distribution-appropriate correlations (Pearson or Spearman) will be calculated as appropriate for each measure and formally tested for statistical significance. These analyses will also be repeated using change from baseline as the outcome rather than the score itself, both as a simple bivariate analysis and using linear regression to model the change as a function of the app usage measures while controlling for baseline values. Analyses will also be repeated using paired *t* tests for differences in HbA_1c_ values from baseline to posttest to measure self-management adherence.

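### H2 is worded both as an association with app usage and as improvement from baseline, and the formal analyses named for the H2 scales serve only the usage association

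*Protocol article*

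**What the plan says.** H2 appears twice in the protocol article.

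- Specific aims textbox, Phase 2: "Measures of app usage will be associated with increased quality of life, self-efficacy, and social support and decreased conflict between the adolescents and their parents".
- Outcome Measures: through app use, self-efficacy, quality of life and perceived social support will improve, and conflict "between the child and parent will be reduced from baseline to 3 months".

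Analysis and Statistical Power calls all analyses exploratory. For all outcomes, which includes the H2 scales, it names the following.

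- Summary statistics, histograms and box plots at each time point, and smoothed plots of trends over the four visits. These are descriptive.
- At each time point, "we will calculate pairwise correlations between the self-management mobile app usage measures and all study outcomes", which are "formally tested for statistical significance".
- The same with change from baseline as the outcome, first bivariate and then "using linear regression to model the change as a function of the app usage measures while controlling for baseline values".

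It then adds one test of mean change, for a single outcome: "Analyses will also be repeated using paired *t* tests for differences in HbA_1c_ values from baseline to posttest".

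Study Design states that there is no control group. Under Study Procedures, the surveys are completed at months 0, 3, 6 and 9.

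**The concern.** The Outcome Measures wording is a statement about mean change within participants, and its null is a mean change of zero. The Specific aims wording is a statement about a gradient across participants, and its null is a usage slope of zero. Either can be true without the other. The formal analyses named for the H2 scales all address the gradient.

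The stake is how the H2 results will be read. If most families improve by a similar amount whatever their usage, every named test is expected to come out null, and H2 could be reported as unsupported. If better-motivated families both use the app more and improve while others worsen, the usage tests can be significant with no average improvement, and H2 as worded in Outcome Measures could be reported as supported. The end of Analysis and Statistical Power also lists, first among the study's primary foci, an effect size to power a larger study. A usage correlation among users does not supply a mean change.

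**Working it through.** **1. What each named analysis tests.** Let D be a participant's change from baseline on an H2 scale and U a usage measure.

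| Analysis named in the plan | Null hypothesis | Specific aims H2 | Outcome Measures H2 |
|---|---|---|---|
| Correlation of U with score | no association with U | yes | no |
| Correlation of U with D | no association with U | yes | no |
| Regression of D on U and baseline | slope on U = 0 | yes | no |
| Paired t test | mean of D = 0 | no | yes, but named for HbA1c only |

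Adding a constant c to every participant's change leaves the correlation as it was: corr(U, D + c) = corr(U, D). The regression slope on U is also unchanged; only the intercept moves, and no test or estimate of the intercept is named. So no size of uniform improvement can affect the named tests of change.

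**2. The plan's own detectable effects.** The plan gives, for 80% power at two-sided 0.05, r = .29 (N=70) and .32 (N=56), and d = 0.30 and 0.34. For the paired t test (noncentral t, df = N−1, noncentrality d√N), two-sided 0.05 gives d = 0.340 and 0.381; one-sided 0.05 gives 0.300 and 0.336. For the correlation (noncentral t), two-sided gives .322 and .356; one-sided gives .288 and .319. The plan's figures therefore match one-sided tests. That is a separate matter, but it means that the two-sided values, d = 0.34 and 0.38, are the ones to use for any added paired analysis.

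**3. Illustration.** The model is D = μ + ρU + √(1−ρ²)·e, with U and e standard normal, so that D has SD 1. There were 20,000 simulated trials per setting, all tests two-sided at 0.05. N = 70 and 56 come from the plan; μ and ρ are assumptions, because the documents give no expected change or usage correlation for the H2 scales.

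| μ | ρ | Paired test rejects, N=70 / 56 | Correlation test rejects, N=70 / 56 |
|---|---|---|---|
| 0.5 | 0 | 98.5% / 95.5% | 4.9% / 5.1% |
| 0.34 | 0 | 80.1% / 70.7% | 4.8% / 5.0% |
| 0 | 0.29 | 5.0% / 5.1% | 69.5% / 59.2% |
| 0 | 0.33 | 5.1% / 5.0% | 81.0% / 71.3% |
| −0.3 | 0.4 | 69.7% / 59.6% (mean worsening) | 93.8% / 87.2% (favourable direction) |

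Hand checks:

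- Paired test, μ = 0.5, N = 70: 0.5 × √70 = 4.18; less the critical value 1.995 leaves 2.19; Φ(2.19) ≈ 0.986.
- Paired test, μ = 0.5, N = 56: 0.5 × √56 = 3.74; less 2.004 leaves 1.74; Φ(1.74) ≈ 0.959.
- Correlation test, ρ = 0.3, N = 70: arctanh(0.3) × √67 = 0.3095 × 8.185 = 2.53; less 1.96 leaves 0.57; Φ(0.57) ≈ 0.72.
- Correlation test, ρ = 0.3, N = 56: 0.3095 × √53 = 2.25; less 1.96 leaves 0.29; Φ(0.29) ≈ 0.61 (62% by simulation).

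**The case against.** The strongest reply is that the formal list of hypotheses is the Specific aims textbox, that H2 there is an association with usage, and that the planned correlations and regressions match it. The Outcome Measures sentence could then be a loose restatement, since it too refers to improvement through use of the app. This stands in part. A reader might infer that H2 is purely a mean-improvement hypothesis and that the wrong analysis was chosen; the documents do not support that, because H2 is stated both ways and one way is served. The Outcome Measures sentence nevertheless gives a direction and an interval from baseline, which a usage slope does not address.

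Second, mean change is not ignored. Summary statistics and trend plots are planned for every measure, all analyses are exploratory, H2 concerns secondary outcomes, and no decision rule is set. A uniform gain of 0.5 SD would probably show in those outputs. This stands and lowers the weight of the point. But the correlations are to be formally tested, while change in the H2 scales has no named test or interval.

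Third, the simulation partly returns its own inputs: a correlation test rejects 5% when ρ = 0, and a paired test 5% when μ = 0, by construction. This is correct. The figures show that the two questions separate; they do not predict what this study will find.

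Fourth, much detail is properly left to a fuller plan. That covers how each scale is summarised. It does not cover two conflicting wordings of one hypothesis, or a mean-change test assigned to HbA1c alone.

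Fifth, a single-arm paired change cannot separate the app from time or study participation. This stands, and the fix must say so.

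**Conclusion.** The point holds as an inconsistency between two wordings of H2, only one of which has a matching formal analysis. It should be corrected, but it does not threaten the study. That conclusion follows from the two null hypotheses and needs no numerical assumption.

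The size is illustrative and rests on normal data, one usage measure and assumed values of μ and ρ. A uniform gain of 0.5 SD unrelated to usage is picked up about 5% of the time by the correlation test, against about 98% (N=70) or 96% (N=56) by a paired test. With zero mean change and a usage correlation of 0.3, the correlation test is significant in about 72% (N=70) or 62% (N=56) of trials.

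A reader might divide those last figures by the nominal 5% and infer a type I error 12 to 14 times too high. The documents do not support that reading: under the Specific aims wording, those rejections are correct detections of a real association, so the figures are power. The fault lies in applying that result to the other wording.

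**What to change.** 1. In the Specific aims textbox and in Outcome Measures, state H2 identically in two parts: H2a, mean change from baseline in each secondary outcome; H2b, association of that outcome or its change with app usage.
2. In Analysis and Statistical Power, add as the analysis for H2a the paired mean change with a 95% confidence interval, for each H2 scale and each respondent, from baseline to month 3 (the interval that Outcome Measures states), and the same at month 6 as a further time point.
3. Keep the usage correlations and regressions as the analysis for H2b.
4. State that, with no control group, the mean change cannot be attributed to the app.

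The cost is wording and some extra output from surveys already scheduled; no participants or visits are added. At two-sided 0.05 with 80% power, the paired analysis detects a standardised change of 0.34 (N=70) or 0.38 (N=56).

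The downside is more exploratory comparisons. From Table 2, taking both child and parent where either is listed, and general and diabetes-specific quality of life separately, there are 2 + 2 (social support scales) + 1 (self-efficacy) + 2 (quality of life) + 2 (conflict) = 9 per time point, or 18 over the two. Presenting them as estimates with intervals, labelled exploratory, is enough.
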